# The efficacy of the traditional Chinese medicine Jia Wei Niu Bang Zi granule combined with methotrexate in treating active rheumatoid arthritis

**DOI:** 10.1097/MD.0000000000014424

**Published:** 2019-02-08

**Keywords:** active rheumatoid arthritis, Jia Wei Niu Bang Zi granule, methotrexate, randomized controlled trial, traditional Chinese medicine

## Abstract

**Background::**

Rheumatoid arthritis (RA) is a chronic systemic and autoimmune inflammatory disease ending with the destruction of joints. Current therapies can relieve RA symptoms, but some also bring severe adverse events. Therefore, an effective and safe therapeutic strategy remains to be created to benefit patients with RA by large. Jia Wei Niu Bang Zi granule (NBZG) consisting of RA-fighting Chinese herbals has been used in Longhua Hospital in the last several decades. NBZG has potential therapeutic effect on RA, which should be evaluated by larger sample clinical trial.

**Methods::**

A multicenter, randomized, double-blind, placebo-controlled clinical trials will be conducted to determine the efficiency of NBZG in pain relief and joint protection. A total of 120 patients with active RA will be enrolled, and treated with NBZG or placebo for 12 weeks. The primary outcome measurements include rate of American College of Rheumatology (ACR) 50 at 12 weeks’ treatment. The 2nd outcome measurements include rate change of ACR20, ACR70, the disease activity score (DAS) 28, 36-item Short-Form Health Survey Questionnaire, Health Assessment Questionnaire - Disability Index, score changes of Patient Assessment of Arthritis Pain, Patient Global Assessment of Arthritis, and the Athens insomnia scale at the same time points.

**Discussion::**

Although NBZG has shown efficacy in treating RA in Longhua Hospital for decades, the universality of this efficacy needs evaluated. The results of this trial will provide a convincing evidence about NBZG's efficacy in treating active RA in a large population.

**Trial registration::**

ClinicalTrials.gov ID: NCT03173040 (registered on May 30, 2017)

## Introduction

1

Rheumatoid arthritis (RA) is a chronic inflammatory joint disease, which usually causes progressive joint destruction, premature unemployment, physical disability, and short-life expectancy.^[1–3]^ Treatment procedures include measuring disease activity with comprehensive indexes, applying treatment-to-target strategy with conventional, biologic (or nonbiologic) disease-modifying antirheumatic drugs. When the disease symptoms remit and stabilize (e.g., showing a low activity), the dose is reduced. With this treatment, most patients with RA show a favorable outcome, but many still do not respond appropriately. Therefore, novel treatments are urgently demanded.

For centuries, herbal medicine has been used as a complementary and alternative medicine for western medicine in China.^[4,5]^ According to the theory of traditional Chinese medicine (TCM), RA can be defined as a Bi syndrome. To deal with RA, Jia Wei Niu Bang Zi decoction (JWNBZ) was established by a group of TCM doctors in China, using fructus arctii as the principal element, and *Bombyx batryticatus*, pseudo-ginseng radix angelicae tuhuo, large Leaf Gentian and *Pinellia ternata* as adjuvant components. JWNBZ could reduce synovial inflammation, bone erosion, and osteoclast number at ankle joints in TNF-Tg mice without triggering any side effect,^[6]^ suggesting the therapeutic potential of JWNBZ against human RA. But this efficacy should be verified with more researches.

We will conduct a well-designed, randomized, double-blind, placebo-controlled trial to estimate the effectiveness and safety of JWNBZ on RA. The outcomes of this clinical trial can evidence the value of JWNBZ to weak disease activity and protect joints from deformity. To guarantee the quality of medicine during the whole trial, we will use JWNBZ granule (NBZG), raw extraction of NBZG decoction, to replace medicinal broth.

## Materials and methods

2

### Ethical issues

2.2

The trial will be conducted in accordance with the Declaration of Helsinki and Ethical Guidelines for Clinical Research, and the trial protocol has been approved by the Research Ethical Committee of Longhua Hospital, affiliated to Shanghai University of Traditional Chinese Medicine, Shanghai, China (approval number: 2017LCSY011), The First Affiliated Hospital of Anhui University of Chinese Medicine (approval number: 2018AHKYBF01), Shanghai Seventh People's Hospital (approval number: 2018-IRBQY-007), and Bengbu Hospital of Chinese Medicine (Approval Number: 2018-BBZYY006) (additional files 1–4). And the protocol has been registered on Clinical Trials (ClinicalTrials.gov, ID: NCT03173040).

### Study participants

2.3

Participants will be recruited from 4 hospitals (Longhua Hospital Affiliated to Shanghai University of Traditional Chinese Medicine, The First Affiliated Hospital of Anhui University of Chinese Medicine, Shanghai Seventh People's Hospital, and Bengbu Hospital of Chinese Medicine). Recruitment poster and website advertisements will be publicized. The planned recruitment period is 12 months.

### Sample size calculation

2.4

We calculated the sample size according to our primary study. We conducted a preliminary experiment from November 2016 to July 2017 into the efficacy of the NBZP combined with MTX vs MTX alone, and we found that patients taking the NBZP combined with MTX achieved 84.8% American College of Rheumatology (ACR) 50, whereas patients in the MTX group achieved 55.5% ACR50 response. The formula to calculate the rate in completely random design is: 

n1 and n2 are the patient numbers in NBZG group and placebo group; 
[figure not shown]
 when type 1 error is 0.05, *u*_*β*_ = 1.282 when type II error is 0.1 in 2-sided tests. 

 is the mean of *p*_1_ and *p*_2_.^[7]^ Approximately 120 participants are needed to achieve a 90% power and a (2-sided) 5% significance level in detecting the therapeutic differences between 2 groups. Thus, the final sample size has been set as 120 patients (60 per group), considering 20% dropout rate.

### Criteria

2.5

#### Inclusion criteria

2.5.1

Participants meeting the following criteria will be included.

Having an age of ≥18 years.Meeting ACR/European League Against Rheumatism criteria for RA, 2010.^[8]^Showing symptoms within 12 months before enrollment.Showing high disease activity at enrollment (disease activity score [DAS] 28 score > 3.2),^[9]^ no prior exposure to oral glucocorticoids (>10 mg/d) or biologic agents.Being able to understand or sign an informed consent form.

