#### Primary outcomes

2.8.1

The ACR50 rate after 12 weeks’ treatment was compared to that at baseline in the 2 groups. The ACR50 is a scale to measure change in RA symptoms,^[10]^ which have been used for testing the effectiveness of clinical interventions in large-sample groups,^[11,12]^ ACR 50 is met when the number of tender joints reduces by ≥50%, the number of swollen joints by ≥50%, and at least 3 of the following 5 indexes improved by ≥50%:

Patient's arthritis pain using a visual analog scale (VAS) of 0 to 100 mmPatient's disease activity using VAS (0–10)Patient's physical function and disability using Health Assessment Questionnaire - Disability Index (HAQ-DI)Acute-phase reactant value such as erythrocyte sedimentation rate (ESR) or C-reactive protein level

Similarly, ACR20 is met when ≥20% is achieved in the reduction of tender joint number, swollen joint number, and the rise of the score of at least 3 of another 5 indexes.

Although compared to ACR50 and ACR70, ACR20 has been accepted as a benchmark in RA clinical trials for its capacity to distinguish active treatment from placebo control,^[13,14]^ ACR50 is still a preferred cutoff than ACR70 to evaluate RA.^[11]^ Here, we choose ACR50 to measure the primary outcome.^[11,15]^

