### Secondary outcomes

2.9

The secondary outcome parameters include the DAS28, rate of ACR20/70, HAQ-DI, 36-item Short-Form Health Survey Questionnaire (SF-36), Patient Assessment of Arthritis Pain, Patient Global Assessment of Arthritis, and Athens insomnia sleep scale.

#### DAS28: from baseline to weeks 4, 8, 12, and 16

2.9.1

The DAS28, a widely used indicator to evaluate RA disease activity after treatment, was published in 1993 by van der Heijde et al.^[16]^ DAS includes the following 4 measurements^[17]^: the counts of swollen and painful joints, the ESR, and a measurement for general health (GH). The formula of DAS28 is 

 The 28 joints include 10 proximal interphalangeal joints and 10 proximal interphalangeal joints of hands and wrists, elbows, knees, and shoulders bilaterally. GH is patient GH VAS (0–10 mm). Using this formula, DAS28 <2.6 signifies remission.

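### Entry sets a DAS28 threshold but no minimum joint counts, so a patient who cannot meet the primary ACR50 endpoint can be randomised

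*Protocol article*

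**What the plan says.** Section 2.5.1 (Inclusion criteria) of the protocol article sets one disease-activity threshold: "Showing high disease activity at enrollment (disease activity score [DAS] 28 score > 3.2". The other disease-related requirements are "Meeting ACR/European League Against Rheumatism criteria for RA, 2010" and symptoms within the 12 months before enrolment. Neither 2.5.1 nor 2.5.2 (Exclusion criteria) gives a minimum number of tender or swollen joints.

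Section 2.9.1 lists the DAS28 components as "the counts of swollen and painful joints, the ESR, and a measurement for general health (GH". It prints the last scale as "GH is patient GH VAS (0–10 mm".

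Section 2.8.1 (Primary outcomes) defines response at 12 weeks: "ACR 50 is met when the number of tender joints reduces by ≥50%, the number of swollen joints by ≥50"%, together with at least three further indexes. Both joint conditions must hold. The article gives no rule for a joint count of zero at baseline.

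Section 2.4 (Sample size calculation) plans on pilot results: "patients taking the NBZP combined with MTX achieved 84.8% American College of Rheumatology (ACR) 50" and "patients in the MTX group achieved 55.5% ACR50 response".

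**The concern.** The entry rule uses a composite score, while the primary endpoint uses two of its components separately. A high ESR, a poor general health score or many joints of one kind can carry DAS28 past 3.2 when the other joint count is zero. A count of zero cannot fall by 50%, so under 2.8.1 as written no treatment effect can make that patient a responder.

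At stake is sensitivity. Each such patient lowers the ACR50 rate of the arm he or she falls in, and the planned difference shrinks in proportion to their share.

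**Working it through.** **1. Can a patient with a zero count pass DAS28 > 3.2?** The DAS28 formula is not readable in the article, so the usual DAS28-ESR coefficients are assumed:

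DAS28 = 0.56√(tender) + 0.28√(swollen) + 0.70 ln(ESR) + 0.014 GH

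The joint counts and ESR values are illustrative. GH is entered as 50 (a 0–100 scale) and as 5 (the 0–10 scale printed in 2.9.1).

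| Tender | Swollen | ESR | GH | DAS28 | Passes? |
|---|---|---|---|---|---|
| 4 | 0 | 20 | 50 | 1.12 + 0 + 2.10 + 0.70 = 3.92 | yes |
| 4 | 0 | 20 | 5 | 1.12 + 0 + 2.10 + 0.07 = 3.29 | yes |
| 0 | 4 | 20 | 50 | 0 + 0.56 + 2.10 + 0.70 = 3.36 | yes |
| 0 | 4 | 20 | 5 | 0 + 0.56 + 2.10 + 0.07 = 2.73 | no |
| 0 | 0 | 40 | 50 | 0 + 0 + 2.58 + 0.70 = 3.28 | yes |
| 0 | 0 | 40 | 5 | 0 + 0 + 2.58 + 0.07 = 2.65 | no |

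Solving DAS28 = 3.2 for ESR with GH = 5 gives these thresholds:
- 4 tender, 0 swollen: exp((3.2 − 1.12 − 0.07)/0.70), about 18.
- 0 tender, 4 swollen: exp((3.2 − 0.56 − 0.07)/0.70), about 39.
- 0 tender, 0 swollen: exp((3.2 − 0.07)/0.70), about 87.

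The patient with no swollen joint therefore passes at a modest ESR on either scale. The patient with no tender joint passes readily on 0–100 and needs a higher ESR on 0–10. The patient with no active joint passes at ESR 40 only on 0–100.

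**2. Reproducing the planned sample size.** Inputs from 2.4: p1 = 0.848, p2 = 0.555, two-sided 5%, 90% power. Here p̄ = 0.7015 and q̄ = 0.2985.

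n = [1.96√(2p̄q̄) + 1.282√(p1q1 + p2q2)]² / (p1 − p2)² = (1.268 + 0.786)² / 0.293² ≈ 49.1, so 50 per group.

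50 × 1.2 = 60 per group, or 120 in all. The stated figure is reproduced and is not in dispute here.

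**3. Cost if a share f cannot respond.** Multiply both rates by (1 − f), which supposes that the pilot rates contain no such patients. Then

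power = Φ{[d√n − 1.96√(2p̄q̄)] / √(p1q1 + p2q2)}, with d = p1 − p2 and n = 60.

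| f (assumed) | Rates | Difference | Power |
|---|---|---|---|
| 0 | 0.848 vs 0.555 | 29.3 points | 0.95 |
| 5% | 0.806 vs 0.527 | 27.8 points | 0.91 |
| 10% | 0.763 vs 0.500 | 26.4 points | 0.86 |

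For f = 0: (0.293 × 7.746 − 1.268)/0.613 = 1.63, and Φ(1.63) = 0.95. On this basis power reaches 0.90 at f of about 6%, and at 1–3% it is 0.94 to 0.93.

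With 50 per group, the number before the dropout allowance, power is 0.90 at f = 0, 0.85 at 5% and 0.79 at 10%.

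**The case against.** The strongest objection is that the problem may be rare. The documents give no share of patients with a zero count, and at 60 per group power stays above the planned 90% until the share reaches about 6%. The other entry criteria, above all the 2010 classification criteria, may make a zero swollen count less common. The article does not reproduce their content or tie them to joints active at Visit 1, so how far they close the gap cannot be judged from it. This objection stands as far as size is concerned. It does not remove the gap in the written rule.

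The power loss also depends on the pilot. If the pilot enrolled under the same rule, its rates already include any such patients and the planned difference does not shrink. Section 2.4 does not state the pilot's entry criteria.

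A convention for scoring a zero baseline count could be set in an analysis plan that is not shown, and its absence from the article is no finding. Eligibility is a different matter: the article lists its criteria, and a scoring rule cannot change who has been randomised.

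Four stronger readings are tempting and are not supported:
- **A biased comparison.** Allocation is randomised 1:1 within centre, so these patients are expected in both arms alike.
- **A breach of intention-to-treat.** Section 2.14 states that approach, and nothing says that these patients would be dropped. Under 2.8.1 as written they are simply non-responders.
- **Routine entry with no active joint at all.** On the printed 0–10 GH scale this needs an ESR above about 87.
- **A need for a floor above one joint.** Resolution of a single joint is a valid fall of at least 50%, so a higher floor is a preference.

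**Conclusion.** The point holds as a gap between entry rule and endpoint. As written, 2.5.1 and 2.5.2 admit a patient with no swollen joint, or with no tender joint, and 2.8.1 makes ACR50 unattainable for that patient. The consequence is a diluted difference and some loss of power.

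The size cannot be fixed from the documents. The figures of 0.91 at 5% and 0.86 at 10% are a sensitivity range. They rest on assumed shares, on non-responder scoring, and on pilot rates free of such patients. The worked DAS28 values rest on assumed coefficients.

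A reader might infer from the word "high" in the criterion that enrolled patients must have many active joints. The threshold does not require that: it lies 0.6 above the article's own remission cut of 2.6. The label is a clerical matter and does not change who is enrolled.

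This is a cheap improvement that should be made. It is not a defect that invalidates the trial.

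**What to change.** Add one line to section 2.5.1: at least 1 tender joint and at least 1 swollen joint at Visit 1, counted on the same joint set that is used for ACR50. One of each is the minimum for both parts of the endpoint to exist; any higher floor is for the sponsor to decide.

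No new data are needed, because both counts are already required at baseline for DAS28 and ACR50. The cost is that a few candidates are screened out and recruitment may be slightly slower. The line must be in place before recruitment starts, since it cannot be applied to patients already randomised.

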#### Exclusion criteria

2.5.2

Presenting autoimmune or inflammatory disease at joints such as adjuvant arthritis, lupus arthritis, osteoarthritis, gouty arthritis, ankylosing spondylitis, infectious arthritis, psoriasis arthritis, enteropathy arthritis, Sjogren syndrome, scleroderma, and cancer.Showing abnormal liver and kidney function.Being pregnant or having a plan of pregnancy (breast feeding women).Presenting severe chronic or acute disease that may drop the patients out.Being addictive to alcohol.

#### Interventions

2.5.3

In NBZG group, patients will be instructed to dissolve NBZG (4 g) in 200 mL hot water and take the solution orally twice a day for 12 weeks, while patients in the placebo group will take NBZG placebo in the same way. Besides, patients in the 2 groups will be given MTX (5 mg per week), and glucocorticoid (<5 mg a day) if necessary, but not any other drugs, especially herbs.

The NBZG will be manufactured, packaged, and labeled by PuraPharm Corporation in Nanning. The crude herbs, including fructus arctii (Niu Bang Zi, 12.1 kg), *B batryticatus* (Jiang Can, 12.1 kg), *Panax notoginseng* (San Qi, 12.1 kg), *Angelica biserrata* (Du Huo, 12.1 kg), Radix Gentianae Macrophyllae (Qin Jiao, 7.9 kg), and Rhizoma Pinelliae (Ban Xia, 12.1 kg), will be supplied in 1 batch from Longhua Hospital and stored in a specialized cool and dry place. NBZG is made from the following ingredients: Fructus Arctii (chaoniubangzi, 9 g), Bombyx Batryticatus (Jiang Can, 9 g), Notoginseng Radix Et Rhizoma (San Qi, 9 g), Angelicae Pubescentis Radix (Du Huo, 9 g), Gentianae Macrop Hyllae Radix (Qin Jiao, 6 g), and Rhizoma Pinelliae (Ban Xia, 9 g). The processes involved are as follows:

1.Extraction: All the herbs mentioned above are put into a water-filled container for a 1-hour soak. And then the mixture is boiled at 100°C for 1 hour. Herbal dregs filtered out, and herbal filtrate collected.2.Concentration: Herbal filtrate is concentrated.3.Granule: Concentrate is mixed with dextrin. The mixture is spray dried to produce dry paste. Then the dry past mixed with magnesium stearate is made into powders, smashed, and screened through a mesh size of 80. Finally, the NBZGs are bagged (4 g per bag). NBZG placebo contains 10% NBZG and 90% bitterant, lactose edible essence, pigment (such as lemon yellow, caramel pigment, and sunset yellow) and starch, and exhibit shape, smell, color, and taste similar to those of NBZGs. For the control group, placebo granules are also made from dextrin (90%) and NBZG (10%) to achieve the same color, smell, taste, and texture as NBZG.

Participants can orally take glucocorticoid <5 mg a day if necessary. At baseline (Visit 1), patients begin to take NBZG or placebo NBZG and laboratory tests. At weeks 4, 8, and 12, patients will visit again (Visits 2 and 4) and perform laboratory tests. Then at week 16, the final visit (Visit 5) will be taken through a phone call. Every patient should visit within 3 days after the arranged time point.

We will call the patients to take laboratory tests to record in a notebook the medicine they have used. When serious adverse effects occur, we will provide an appropriate treatment to the patient immediately, record the adverse effect, and stop medicine.

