### Safety assessments

2.10

To assure the safety of participants, the data collection process will be supervised by the project director. The patients’ blood routine, urine routine, feces routine, kidney, and liver function will be tested on schedule. At each visit, patients will be asked about the adverse effects during the study period. To protect their privacy, all participants will be visited in a closed room. Participants can raise questions and withdraw at any time.

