### Data collection and monitoring

2.12

During this 16-week trial, all participants will be treated with NBZG or NBZG placebo for 12 weeks follow-up for 4 weeks. Five rounds of disease activity assessments (the baseline, week 4, week 8, week 12, and week 16) and 5 rounds of safety assessments (the baseline, week 4, week 8, week 12, and week 16) will be recorded in Epidata (Version 3.1) by 2 statisticians independently. Disagreement will be solved by discussion and a third statistician.

Longhua Hospital Affiliated to Shanghai University of Traditional Chinese Medicine (http://www.longhua.net/ywsy/gzlc/287.jhtml) control the quality.

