### Statistical analysis

2.14

All data analyses will be performed using Statistical Packages of Social Sciences (SPSS) software (version 22.0). Continuous data are presented as mean ± standard deviation (SD) and categorical data as frequencies. Continuous variables following the normal distribution will be analyzed by Student *t* test; otherwise, nonparametric tests will be used to compare group differences. Statistical test is 2-sided and *P*-value <.05 will be defined as statistically significant. We will adopt intention-to-treat approach and last-observation-carried-forward method will be applied in the missing values.

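### DAS28 is scheduled at week 16, but the week-16 visit is a phone call; if the call governs, that secondary time point cannot be measured, and the stated LOCF rule would copy an earlier value into it

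*Protocol article*

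**What the plan says.** All references are to the protocol article.

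- **Visit mode (2.5.3 Interventions).** On the clinic visits after baseline: "At weeks 4, 8, and 12, patients will visit again (Visits 2 and 4) and perform laboratory tests". On the last visit: "Then at week 16, the final visit (Visit 5) will be taken through a phone call".
- **DAS28 (2.9.1).** The heading gives the time points: "DAS28: from baseline to weeks 4, 8, 12, and 16". The components are "the counts of swollen and painful joints, the ESR, and a measurement for general health (GH").
- **Assessment rounds (2.12 Data collection and monitoring).** For disease activity the plan has "Five rounds of disease activity assessments (the baseline, week 4, week 8, week 12, and week 16"). Safety has its own count, at the same five time points: "5 rounds of safety assessments (the baseline, week 4, week 8, week 12, and week 16").
- **Safety content (2.10 Safety assessments).** Laboratory work is described as "blood routine, urine routine, feces routine, kidney, and liver function will be tested on schedule". The same section says that patients are asked about adverse effects at every visit.
- **Missing data (2.14 Statistical analysis).** Under intention-to-treat, the "last-observation-carried-forward method will be applied in the missing values", with no exception by outcome or visit.

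**The concern.** The visit mode and the list of week-16 measurements cannot both be carried out as written. A swollen and tender joint count needs an examiner, and an ESR needs a blood sample. Neither can be had by telephone.

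Section 2.12 describes 12 weeks of treatment followed by 4 weeks of follow-up, so week 16 is the only scheduled assessment after treatment ends. A week-16 DAS28 that was never measured, but was filled in by the general missing-data rule, would appear in a results table like any other time point. A reader could take it as a maintained effect. In addition, four hospitals take part. If the text is left as it is, some may telephone and others may bring patients in, and the availability of week-16 data would then depend on the centre.

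**Working it through.** The plan gives no figure on this point to reproduce. The check sets the statements side by side and then follows the missing-data rule through.

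**Step 1. What a week-16 phone call can supply**

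| Week-16 item | Where planned | Obtainable by phone? |
|---|---|---|
| Swollen joint count (DAS28) | 2.9.1 | No |
| Painful joint count (DAS28) | 2.9.1 | No: an examined 28-joint count |
| ESR (DAS28) | 2.9.1 | No; 2.5.3 lists no week-16 laboratory tests |
| General health VAS (DAS28) | 2.9.1 | Only in a suitable form |
| HAQ-DI, AIS, SF-36 | 2.9.2, 2.9.4, 2.9.5 | Yes, in principle |
| Pain and global VAS | 2.9.3 | Only in a suitable form |
| Adverse-event questions | 2.10, 2.12 | Yes |
| Blood, urine, feces, kidney and liver tests | 2.10, 2.12 (if part of the round) | No |

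Three of the four DAS28 components are unavailable, so the score cannot be computed. This follows from the visit mode and not from patient behaviour, so it applies to all patients in both groups: 60 + 60 = 120.

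**Step 2. Whether other text removes the conflict**

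- The end of 2.5.3 mentions calling patients in connection with laboratory tests. It gives no time point, and even if it means calling patients in for tests, it supplies no joint counts.
- The same section asks every patient to visit within 3 days after the arranged time point. It does not say that this turns Visit 5 into a clinic visit.
- Table 1, the assessment schedule, is not shown. Whatever it contains, the text of 2.5.3 and that of 2.9.1 disagree.

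**Step 3. What literal carry-forward would do**

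Let Y12 and Y16 be a patient's DAS28 at weeks 12 and 16 in the analysis data set, with Y16 never observed.

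- Patient seen at week 12: Y16 = Y12, so Y16 − Y12 = 0.
- Patient last seen at week 4 or 8: that value fills both week 12 and week 16, so Y16 − Y12 = 0.
- Patient with baseline only: the baseline value fills both, so again 0. A baseline value should exist for everyone, because 2.5.1 requires DAS28 above 3.2 at enrollment.

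Every patient's week-16 value then equals the week-12 analysis value. Group means, standard deviations and the between-group test (t test or nonparametric) at week 16 are therefore identical to those at week 12.

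**Step 4. What is not touched**

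The primary outcome (2.8.1) is ACR50 after 12 weeks of treatment, and the sample size of 120 (2.4) is based on ACR50 rates. Neither uses week 16.

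**The case against.** The best counter-argument is that the conflict is narrow and its consequences are conditional. Most of that stands.

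- **A reader might infer that the fifth safety round cannot be done at all.** The text does not support this. Section 2.10 includes adverse-event questions at each visit, and its laboratory tests follow a schedule that 2.5.3 sets at baseline and weeks 4, 8 and 12. A week-16 round consisting of adverse-event enquiry by phone fits all three sections. What is lacking is a statement that the round is limited to that.
- **A reader might infer that all week-16 disease-activity data are lost.** Section 2.12 does not list what a disease-activity round contains, and the questionnaires scheduled at week 16 can be collected remotely. DAS28 is the outcome that clearly cannot.
- **A reader might infer that the plan intends to claim durability from carried-forward data.** No section plans a week-12 to week-16 comparison or a test of maintained effect. Section 2.14 gives one general sentence on missing values and does not name week 16. An analysis plan that is not shown may treat assessments that were never performed differently.
- **A reader might take 120 of 120 missing as fact.** It holds only if the phone-call sentence governs. If 2.9.1 and 2.12 reflect the intended schedule and 2.5.3 is loosely worded, nothing need be missing.

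None of this removes the contradiction between 2.5.3 and 2.9.1. An analysis plan cannot recover joint counts and ESR values that were not collected.

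**Conclusion.** The concern holds in limited form: section 2.5.3 conflicts with section 2.9.1, and with the week-16 disease-activity round in 2.12 so far as that round includes DAS28.

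The size of the problem rests on two assumptions. If the phone call governs, week-16 DAS28 is unmeasurable for every patient. If the carry-forward rule is also applied literally, the week-16 DAS28 comparison duplicates week 12 and carries no post-treatment information. On the same first assumption, post-treatment laboratory safety is not observed at week 16, while adverse events can still be recorded.

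Severity is moderate: one time point of one secondary outcome, plus an undefined week-16 safety round. The finding does not weaken the primary analysis.

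**What to change.** Reconcile 2.5.3 with 2.9.1 and 2.12, and make Table 1 agree. Which statement reflects the intended visit is for the sponsor to say.

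If Visit 5 stays a phone call:

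1. Remove week 16 from the DAS28 time points.
2. State in 2.10 and 2.12 that the week-16 safety round is adverse-event enquiry only.
3. Limit week 16 to measures that can be collected remotely: HAQ-DI, AIS and SF-36, and the VAS scores only if a suitable form is specified.
4. State in 2.14 that DAS28 and laboratory values are not carried forward from week 12 to week 16.

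This costs a wording amendment and the loss of a week-16 DAS28 time point that was nominal in any case. If the sponsor instead confirms that week-16 DAS28 is to be measured, the description of Visit 5 must change. The cost is then one further clinic visit per patient, at most 120, or 120 × 0.8 = 96 at the 20% dropout assumed in 2.4. Either way, the change should be made before the first patient reaches week 16, because measurements not taken then cannot be recovered.
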